For cost-utility as primary health-economic outcome measure, we anticipate a clinically relevant 0.1 gain in QALYs for the enhanced therapy group with group standard deviations for QALYs of 0.15 [64]. We use an estimation of cost difference of €0 per participant between both groups with group standard deviations for costs of €1000 [65, 66]. We allow room here for a more positive outcome in costs, as we predict an average cost saving per participant of €1113.75 for enhanced therapy based on the expected clinical effect of 59% relative reduction in number of ulcers compared with usual care (see Table 1). With a willingness to pay (WTP) of €50,000, a correlation between costs and QALYs (*ρ*) of 0, *α* = 0.05 (two-sided), power = 80%, and a drop-out rate of 20%, this leads to a sample size of 63 participants per study group, or 126 participants in total. Without drop-out, a sample size of (63 × 0.8 =) 51 participants per study group or 102 in total is required.

**Table 1 Tab1:** Average predicted costs per participant

				**Enhanced therapy**		**Usual care**	
**Modality**	**Event/activity**	**Time (hours)**	**Unit costs**	**Expected frequency**	**Expected costs**	**Expected frequency**	**Expected costs**
	Ulcer development [6]	-	€10,000	0.15	€1500	0.37	€3700
	Podiatrist	1	€100	0.50	€50	0.00	€0
Custom-made footwear	Optimization equipment: pressure measurements [36]	-	€50	1.00	€50	0.00	€0
	Shoe technician	1	€100	2.00	€200	0.00	€0
Custom-made indoor footwear	Production and optimization [13]	-	€400	0.95	€380	0.00	€0
Personalized temperature monitoring	Thermometry [38]	-	€75	0.75	€56.25	0.00	€0
Personalized education	Structured education	1	€100	0.50	€50	0.00	€0
	Motivational Interviewing	1	€100	2.00	€200	0.00	€0
	Equipment [49, 57]	-	€100	1.00	€100	0.00	€0
**Total**					€2,586.25		€3,700

Average of predicted additional costs per participant of enhanced therapy versus usual care, based on the expected frequencies as described in the power calculation. For all costs except ulcer development, usual care is used as index. Unit cost estimations are based on previous studies and standard hourly wages of a college educated professional in the Netherlands

With the power calculations showing a requirement of 122 participants for the primary clinical outcome, 120 for the primary patient-related outcome, and 126 for the primary health-economic outcome, a sample size of 126 participants provides adequate power for all three primary outcomes.

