### Strengths and limitations

A strength of this trial is being powered for three primary outcomes, including a clinical outcome (foot ulcer recurrence) generally used in foot ulcer prevention trials [15], a patient-related outcome (footwear adherence) that captures the patient’s perspective, and a health-economic outcome (cost-utility). This combination of perspectives is a major strength, as it can offer evidence in multiple directions. Especially including cost-utility as one of the primary outcome measures is a strength, as this is hardly investigated in this field, despite frequent calls for insights into health-economy [7]. Since personalization requires more time from healthcare professionals, the intervention will incur extra costs. Furthermore, the use of assistive devices and sensors also increases costs. It is therefore necessary to investigate whether the benefits outweigh the extra costs. Both cost-utility and cost-effectiveness are included as outcomes in this trial. Cost-utility has been chosen over cost-effectiveness because of its generalizability, as QALYs are a universal measure for which the willingness to pay can be determined independent of the patient population [45]. Cost-utility is also used as the primary outcome for the sample size calculation, which deviates from how most clinical studies conduct a sample size calculation, taking ulceration as primary outcome. We chose cost-utility, as this may be seen as a more important outcome than ulceration alone, because it takes the quality of life of participants and the costs into account, with changes in ulcer outcome being negotiated in these personal and health economic outcomes. Another strength is the focus on a personalized and state-of-the-art approach, to use the latest evidence on effective treatment and to consider this treatment with respect to usability and effectiveness for the individual patient, thereby reducing patient burden and increasing treatment adherence where possible.

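### The cost-utility sample size that sets N = 126 does not follow from its printed inputs, which give 36 per group before drop-out (90 in total after it), not 51 (126)

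*Protocol article*

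**What the plan says.** The cost-utility paragraph of Sample size {14} prints a full set of inputs:

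- QALYs: "we anticipate a clinically relevant 0.1 gain in QALYs for the enhanced therapy group", with "group standard deviations for QALYs of 0.15".
- Costs: "We use an estimation of cost difference of €0 per participant between both groups with group standard deviations for costs of €1000".
- Willingness to pay (WTP) €50,000, correlation between costs and QALYs 0, two-sided alpha 0.05, power 80%, drop-out 20%.

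It concludes that "this leads to a sample size of 63 participants per study group, or 126 participants in total", and that without drop-out "51 participants per study group or 102 in total is required". The section closes by comparing the three requirements (122 for ulcer recurrence, 120 for adherence, 126 for cost-utility), adopts the largest and states that power is adequate for all three primary outcomes. Strengths and limitations confirms the role of this calculation: "Cost-utility is also used as the primary outcome for the sample size calculation".

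**The concern.** Every input needed to repeat the calculation is printed, and so is the result, but the two disagree by 15 per group before drop-out. That is too much for rounding or for the choice between a normal and a t distribution.

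The paragraph fixes the recruitment target and carries the claim of adequate power for the health-economic primary outcome. As printed, that claim cannot be verified. If the inputs are right, cost-utility does not determine N and the article describes its own sizing wrongly. If the result is right, at least one published assumption is not the one used.

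**Working it through.** **Inputs** (Sample size {14}; 1:1 allocation from Trial design {8}): WTP = €50,000; QALY difference 0.1; SD of QALYs 0.15; cost difference €0; SD of costs €1000; rho = 0; two-sided alpha 0.05 (z = 1.960); power 80% (z = 0.8416); drop-out 20%.

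**Method.** Compare mean net monetary benefit between two equal groups.

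- Difference = WTP × QALY difference − cost difference
- SD² = (WTP × SD_QALY)² + SD_cost² − 2 × rho × WTP × SD_QALY × SD_cost
- n per group = 2 × (1.960 + 0.8416)² × SD² / difference²

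**Attempt to reproduce the plan's 51.**

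- Difference = 50,000 × 0.1 − 0 = €5000
- SD = √(7500² + 1000²) = €7566
- n = 15.698 × 7566² / 5000² = 35.95, so 36 per group (37 with the t distribution)
- After drop-out: 36 / 0.8 = 45 per group, 90 in total

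The plan states 51, 63 and 126. With the printed inputs, power at 63 × 0.8 = 50.4 completers per group is 91.3%, and at 51 it is 91.6% (90.7% and 91.1% with the t distribution).

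**Other readings of the method, keeping the printed means and SDs.**

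| Change | n per group |
|---|---|
| One-sided test | 29 |
| Alpha 0.025 | 44 |
| Alpha 0.05/3 | 48 |
| Rank-test inflation | 38 to 42 |
| rho = −1 | 46 |
| 90% power | 49 |

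None gives 51. Only 90% power comes within two patients, and it contradicts the stated 80%.

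**Single-input changes that do give about 51** (all else as printed).

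| Input changed | n before rounding |
|---|---|
| Cost SD €5000 (net-benefit SD €9014) | 51.02 |
| WTP €10,000 | 51.02 |
| QALY SD 0.179 | 50.93 |

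The first two agree exactly because, at zero cost difference, n depends on the cost SD only through its ratio to WTP. Rounded up, 51.02 is 52 per group, and 52 / 0.8 = 65 after drop-out. At 50.4 completers, power with a cost SD of €5000 is 78.7% (t distribution) to 79.5% (normal).

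**Check on the cost SD from Table 1.** The table gives €10,000 per ulcer at expected frequencies 0.37 and 0.15, and no SDs. Assume each ulcer is a fixed cost that a participant either has or does not have:

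- Usual care: 10,000 × √(0.37 × 0.63) = €4828
- Enhanced therapy: 10,000 × √(0.15 × 0.85) = €3571

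On that assumption one cost item alone exceeds €1000 several-fold. Using these two SDs in the formula gives 46.6, so 47 per group.

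**Drop-out conversion.** 63 × 0.8 = 50.4, which the plan rounds to 51; going the other way, 51 / 0.8 = 63.75, which rounds up to 64. This small slip does not explain the main gap.

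**The case against.** The strongest reply is that nothing practical follows. Under the printed inputs 126 is more than cost-utility needs, and it still covers the stated 122 and 120. With a cost SD of €5000 and rho 0 as stated, power is about 79% against a nominal 80%. This stands: the trial's size need not change. It does not remove the contradiction in the calculation that is said to set that size.

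A second reply is that an article condenses the full protocol. That does not help here, since nothing is said to be missing. The inputs and the result are both printed and disagree.

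Two stronger readings are tempting, and the document does not support either.

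- **The cost SD is proven to be the error and should read €5000.** Two other single-input changes fit about as well. Table 1 makes €1000 implausible only under the fixed yes/no cost assumption, and even then points to 47 per group, not 51. The sources cited for the SDs are not visible in the document.
- **The trial is badly underpowered because ulcers raise cost and lower quality of life, so rho is negative.** With a cost SD of €5000 and an assumed rho of −0.3 or −0.5, power at 50.4 per group falls to about 68% or 63%. But the plan states rho = 0 and gives no other value. Those figures also leave out the plan's predicted saving of €1113.75 per participant, which it deliberately set aside by taking the cost difference as €0. With the saving, the difference becomes 5000 + 1113.75 = €6113.75, and power is about 85% at rho −0.3 and 80% at −0.5.

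**Conclusion.** The printed inputs give 36 per group (45 after drop-out, 90 in total), not 51 (63, 126). This rests on the usual net-monetary-benefit comparison of two means, and no conventional variant consistent with the stated alpha, power and correlation closes the gap. At least one printed input or the result is wrong.

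The document does not settle which. The cost SD is the most likely candidate for two reasons: the €50,000 threshold recurs in the analysis section (Primary study outcomes), which makes a slip in WTP less likely, and Table 1 is hard to square with €1000 under the assumption stated above. That is a judgement of likelihood, not a demonstration.

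The consequence is limited. The stated basis for N and the power claim for one of three primary outcomes cannot be verified as published, but neither the printed inputs nor a cost SD of €5000 at rho 0 calls for a different N.

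**What to change.** State the inputs actually used, and make inputs, result and power agree. Keep N = 126.

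- If the cost SD was about €5000, print it, give 52 per group before drop-out and 65 after it, and state power of about 79% at 126 with 20% drop-out.
- If another input differed, print that one and recompute in the same way.
- If the printed inputs are right, restate the requirement as 36 per group (45 after drop-out), say that the ulcer outcome (122) drives N, and amend the sentence in Strengths and limitations to match.

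A line on power under negative rho is optional. If it is given, label rho as an assumption and show power both with the €0 cost difference and with the predicted €1113.75 saving.

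The cost is a wording correction in the Sample size section, with no extra participants and no change to conduct. If the cost SD was about €5000, the stated power becomes about one percentage point less favourable.

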### Recruitment {15}

Patients will be recruited both retrospectively from outpatient visit schedules and prospectively. Recruitment takes place at all participating centers, i.e., Amsterdam UMC (location AMC and location VUmc), Máxima Medisch Centrum (Veldhoven), and Reinier de Graaf Gasthuis (Delft) in the Netherlands. Recruitment will continue until a total of 126 participants have been included and randomized into the study. We anticipate this to take 18 months to complete. Each patient will be followed for 12 months for ulcer development and other outcomes, and for an additional 6 months for ulcer and cost-utility outcomes if an ulcer is present at 12 months’ follow-up.

### Assignment of interventions: allocation

#### Sequence generation {16a}

Participants will be randomly assigned to either enhanced therapy or usual care using an independent method, being an online-accessible computer program (Castor EDC, Amsterdam, the Netherlands) that uses a variable block randomization method. Randomization will be stratified according to participating center (with both locations of Amsterdam UMC seen as 1 center) and time since healing of last ulcer with a gender-specific cut-off (6 months for men and 10 months for women, based on median values of time since healing of last ulcer in a previous study [20]).

#### Concealment mechanism {16b}

The allocation is computer-generated at the moment of randomization using an independently-generated sequence (Castor EDC, Amsterdam, the Netherlands) and therefore concealed until the moment of randomization.

#### Implementation {16c}

The code for allocation sequence will be prepared by a non-involved investigator. Once written, the code is stored in Castor EDC.

### Assignment of interventions: blinding

#### Who will be blinded {17a}

The outcome assessors of the primary clinical outcome (i.e., ulcer or no-ulcer) will be blinded to group allocation. Participants, shoe technicians, and investigators cannot be blinded to group allocation. We aim to blind the involved physicians and podiatrists by not informing them about group allocation; however, because the participant and shoe technician are not blinded, blinding of the involved physicians and podiatrists cannot be guaranteed. Primary statistical analyses will be done by an investigator blinded to group allocation.

#### Procedure for unblinding if needed {17b}

Both the investigator and the participant are not blinded and therefore no procedures for unblinding them are required. Involved physicians and podiatrists can be notified about group allocation by the investigator when deemed necessary. The investigator performing the primary statistical analyses will be unblinded after the analyses are conducted.

### Data collection and management

#### Plans for assessment and collection of outcomes {18a}

The study investigators will perform all study measurements, during baseline, randomization, and follow-up visits. The treating podiatrist or physician will initially assess foot ulcer outcomes (when occurring), including taking photographs of the foot. See Fig. 2 for an overview of the study procedures.

##### Baseline assessments to confirm definitive eligibility

If an eligible participant consents to participate, they will undergo a baseline assessment at the participating hospital to confirm eligibility for inclusion in the study. The following characteristics will be obtained during the baseline visit:Demographic information and disease-related characteristics (e.g., diabetes duration and control, presence of complications, ulcer history, footwear use, etc.).Peripheral neuropathy assessment, consisting of testing for the presence of neuropathy by measuring the loss of protective sensation by using the 10-g (5.07) Semmes Weinstein monofilament at the plantar surface of the hallux and the first and fifth metatarsal heads of both feet, and with a 128-Hz Tuning fork held on the apex of the great toe [31].Peripheral arterial assessment by palpation of the dorsalis pedis and posterior tibial pulses in both extremities, according to the wound, ischemia, and foot infection (WIfI) classification system [60, 61]. Additional vascular assessment will be done by measuring the toe-pressure [60, 61].Presence of foot deformity will be assessed clinically. These include hammer/claw toes, prominent metatarsal heads, hallux valgus, pes planus, pes cavus, Charcot deformity, and any amputation. Participant’s feet will be classified into one of four categories according to the severity of deformity present: no deformity, mild deformity, moderate deformity, and severe deformity [10].

##### Assessments at baseline visit

If eligibility has been confirmed, photographs of the plantar and dorsal surfaces of both feet will be taken according to a standardized protocol [10] and foot-related self-care behavior will be assessed using a 7-item questionnaire based on a commonly used questionnaire by the Dutch Society of Podiatry (Nederlandse Vereniging voor Podotherapie, NVvP) [67]. Quality of life will be assessed by using the SF-36 and EQ-5D-5L questionnaires [5, 46]. Participants will complete a study questionnaire consisting of the following topics: satisfaction with ulcer prevention treatment; use and usability of their custom-made footwear (using a study-specified Monitor Orthopedic Footwear [51]); capabilities, opportunities, and motivations for ulcer prevention using an adapted COM-b questionnaire [54]; and knowledge of foot care (questions 24–29 from the Patient Interpretation of Neuropathy questionnaire [53]).

Furthermore, barefoot plantar pressure distribution during standing and walking will be measured using the Novel EMED-X platform system (Novel GmbH, Munich, Germany), which consists of pressure-sensing sensors (4 per cm^2^) that are sampled at 50 Hz. Four trials of both feet at the subjects’ self-chosen comfortable pace using a “two-step” gait approach to the platform will be collected [68]. In-shoe plantar pressure distribution will be measured inside the two most frequently used pairs of custom-made footwear. In-shoe pressures will be measured with the Pedar-X system (Novel GmbH, Munich, Germany), which comprises flexible pressure-sensing insoles (99 sensors, 50Hz sampling rate) placed between the sock and the shoe insole. Measurements will be performed at a self-chosen comfortable speed along a walkway of at least 10 m; gait speed will be recorded and kept within 10% for all walking trials. A minimum of 12 mid-gait steps per foot will be recorded [69].

Additionally, physical activity and wearing time of the custom-made footwear will be assessed. Physical activity will be measured for seven consecutive days following the baseline visit using a MoveMonitor (McRoberts, the Hague, the Netherlands), worn in a belt around the middle at vertebrae L5 [57]. Participants also receive a short diary for these 7 days to keep track of time points and activities throughout the week. All custom-made footwear will be equipped with a validated temperature sensor in a cavity created underneath the top layer of the shoe insert (OrthoTimer; Rollerwerk, Balingen, Germany) [49]. This will be used to objectively assess footwear use by the participant throughout the trial.

##### Assessments at randomization

Two weeks after study entry, the randomization visit will take place at the orthopedic shoe company. The feet of the participant will be checked for foot ulceration. If a participant has a foot ulcer, they will be immediately referred to the multidisciplinary team, and randomization will be postponed until the ulcer is healed for 2 weeks. If there is no foot ulcer, and all other eligibility criteria are also still met, the participant will be randomized to one of the two study groups.

##### Assessments during follow-up

Each participant will be followed for 12 months. If a participant has a foot ulcer at 12 months, they will be followed for another 6 months or until healing, whichever comes first. Follow-up will take place after 3, 6, 9, and 12 months (FU3, FU5, FU7, and Final visit (FV), respectively). Prior to each regular study visit, all participants will receive the EQ-5D-5L questionnaire and study specified versions of the iMTA iMCQ and iMTA iPCQ to gather volume data on medical costs, family costs, and productivity loss [45]. Additionally, at 6 and 12 months, all participants also complete the study questionnaire (see the section “Assessments at baseline visit”), and at 12 months also the SF-36. Participants in enhanced therapy will hand in their weekly diaries.

Custom-made footwear wearing time will be assessed during each 3-monthly visit by reading out the OrthoTimer sensor in the shoe. At 6 and 12 months, physical activity is assessed by wearing the activity monitor for 1 week. At 12 months, barefoot and in-shoe plantar pressure measurements will be repeated. Use of intramural healthcare resources during the study will be obtained at final visit from the participants’ medical status. If a participant has a foot ulcer at 12 months, visits will be scheduled at 15 and 18 months, or 2 weeks after healing (whichever comes first). During these visits, volume data on medical costs, family costs, and productivity loss will be gathered (iMTA) and the EQ-5D-5L will be completed. An overview of all measurements can be seen in Fig. 2.

##### Unscheduled assessments: foot ulceration

If the participant, treating physician, or podiatrist identifies an ulcer in-between 3-monthly regular visits, they are instructed to inform the investigator immediately, and have photographs taken of the foot by the treating physician or podiatrist. The podiatrist will debride the wound first if required to assess outcome, and will classify the ulcer using the University of Texas Wound Classification [59] and the WIfI-score [60, 61]. This information will be sent to the investigator, who will upload all information anonymously to a web-based environment for ulcer outcome assessment. A panel of blinded and independently operating physicians with > 10 years of experience in diabetic foot care will then assess these photographs. Participants will complete the validated Dutch version of the Cardiff Wound Impact Schedule [55, 56] 4 and 12 weeks after an ulcer occurred, provided the ulcer has not yet healed. Participants will complete the EQ-5D-5L one extra time, 4 weeks after an ulcer occurred, as presence of a foot ulcer is known to reduce quality of life [70]. Participants will then continue with the follow-up assessments as scheduled.

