### Outcomes {12}

There are three primary study outcomes in this study, which are:Foot ulcer recurrence during the 12-month follow-upAdherence to wearing custom-made footwearThe cost (savings) per quality-adjusted life year (QALY) gained (i.e., cost-utility)

These represent a clinical, patient-related, and health-economic perspective, respectively. Foot ulcer recurrence is defined as “a break of the skin of the foot that involves as a minimum the epidermis and part of the dermis, in a person who has a history of foot ulceration, irrespective of location and time since the previous foot ulcer” [15], is monitored during the entire study period, and is—on group level—calculated as the proportion of participants with one or more foot ulcers during the study period. Footwear adherence is defined as the percentage of steps taken in prescribed footwear, calculated by combining physical activity and wearing time measurements [44]. It is calculated over 1 week, at baseline and (for outcomes) at 6 and 12 months’ follow-up. Cost-utility is monitored during the entire study period, costs are summed throughout the 12-month period [45], and utility is scored with the EQ-5D-5L questionnaire every 3 months [46].

Secondary study outcomes are as follows: proportion of participants with one or more recurrent foot ulcers on the plantar side of the foot [15]; proportion of participants with one or more recurrent foot ulcers at the predefined personalized high-risk locations [15]; ulcer-free survival days [47]; falls [48]; wearing time of custom-made footwear [49]; in-shoe peak plantar pressure [47]; cumulative plantar tissue stress [44]; footwear wear-and-tear [50]; ulcer risk prediction score [29]; treatment and footwear satisfaction [51]; foot-related self-care [52]; knowledge of foot care [53]; capabilities, opportunities, and motivations (COM-b) score [54]; quality of life (in participants with [55, 56] or without [5] a recurrent foot ulcer during the trial); physical activity [57]; costs [45]; QALYs [46]; and cost-effectiveness [45]. In participants with an ulcer, other secondary outcomes are as follows: time to ulceration [58], ulcer severity [59–61], time to healing [58], and referral time [62]. Definitions for all secondary outcomes are as provided in the reference following each secondary outcome. All secondary outcomes are monitored during the entire study period using assessments and questionnaires during follow-up visits (see Fig. 2).

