##### Other study outcomes

Differences in costs and QALYs between enhanced therapy and usual care will be assessed using independent samples *T*-tests, with 95% bias-corrected and accelerated confidence intervals around the mean difference to account for sampling variability, stratified for a maximum of two variables that are univariately associated with the outcome. For cost-effectiveness, the approach will be identical to the approach for cost-utility described above, with foot ulcer recurrence as the clinical outcome. For all other study parameters (see the “Outcomes {12}” section), differences between enhanced therapy and usual care will be assessed via independent sample* T*-tests (for normally distributed data) or Mann–Whitney *U*-tests (for not normally distributed data) in case of interval or ratio data, and with chi-square or Fisher’s exact tests in case of nominal or ordinal data.

In addition, a budget impact analysis (BIA) will be done. The budget impact analysis will be carried out from governmental, health care provider, and insurer perspectives. The governmental perspective is chosen to help setting priorities in health care optimization while simultaneously considering the wider implications of stimulating enhanced therapy for diabetic patients at a high risk of ulcers beyond the health care sector. The provider perspective is chosen to support local decisions on economies of scale and affordability. The insurer perspective is chosen to assess the net financial consequences of offering intensified monitoring to high-risk patients who already have had ulcers in the past, which may help to shift health care use from the second to the first echelon. The BIA will be conducted using a decision-tree model developed in Microsoft® Excel. The BIA will be performed according to the Professional Society for Health Economics and Outcomes Research Task Force principles. We will use multiple scenarios with different numbers for the population to target, different treatment adherence, and different implementation scenarios, based on the best estimates available at the time of analysis.

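### The Cardiff Wound Impact Schedule is compared between arms only in participants who ulcerate and are still unhealed, so it is not a randomised comparison and should be reported descriptively

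*Protocol article*

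**What the plan says.** In the protocol article, Unscheduled assessments: foot ulceration, the instrument and its condition appear together: "Participants will complete the validated Dutch version of the Cardiff Wound Impact Schedule" at time points given as "4 and 12 weeks after an ulcer occurred, provided the ulcer has not yet healed". The sentence that follows sets no healing condition for the generic measure: "Participants will complete the EQ-5D-5L one extra time, 4 weeks after an ulcer occurred".

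Outcomes {12} lists as a secondary outcome "quality of life (in participants with [55, 56] or without [5] a recurrent foot ulcer during the trial". References 55 and 56 are the ones attached to the wound schedule, so it is the quality-of-life measure for participants who ulcerate. The same section lists time to healing and ulcer severity as separate outcomes in those participants.

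Statistical methods {20a} says that all tests assess group effects. Other study outcomes then says of every remaining parameter that "differences between enhanced therapy and usual care will be assessed via independent sample" t-tests, or Mann–Whitney tests when the data are not normal. A between-arm test of the schedule follows from these statements. No separate handling of healed ulcers is given. The missing-data section {20c} takes its imputation predictors from baseline characteristics, not from healing status.

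**The concern.** A score exists only if two things happen after randomisation: the participant ulcerates, and the ulcer is still open at week 4 or 12. The intervention is designed to change the first and may change the second. The groups being tested are therefore not the randomised groups, and a difference or its absence cannot be read as a treatment effect on wound-related quality of life.

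The healing condition adds an avoidable layer. If one arm's ulcers heal faster and milder ulcers heal sooner, the ulcers left to be scored in that arm are more severe on average. Its mean impact can then look worse although no participant is worse off.

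This is a data-collection rule, so scores that were never collected cannot be recovered later. If healed participants were treated as missing, a baseline-only imputation model would fill in their scores from people with open wounds.

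**Working it through.** **The plan's own figure.** The article gives no figure for the schedule. The ulcer sample size fixes how many people could ever complete it. With 37% versus 15%, two-sided α = 0.05, 80% power and pooled variance under the null:

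n per arm = [1.96·√(2·0.26·0.74) + 0.842·√(0.37·0.63 + 0.15·0.85)]² / 0.22² ≈ 61.2.

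This agrees with the stated 61 per group, apart from rounding (62 when rounded up; power at 61 is 79.9%).

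**How many people ulcerate.** At 63 per arm: 0.37 × 63 = 23.3 in usual care and 0.15 × 63 = 9.5 in enhanced therapy, about 33 in all.

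**Selection by healing.** The documents give neither healing times nor a healing difference, so these inputs are assumptions:
- Severity S is standard normal and identically distributed in both arms.
- Healing time is exponential with rate (ln 2 / median) × HR × exp(−b·S). The median is 8, 12 or 20 weeks; b is 0, 0.5 or 1.0; HR (faster versus slower arm) is 1.0, 1.5 or 2.0.
- The score has correlation 0.7 with severity, and there is no true arm difference at equal severity.

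A simulation of 1,000,000 ulcers per arm compared mean scores among ulcers still open. The table gives the shift against the faster arm over all three medians with b = 0.5 or 1.0:

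| HR | Week 4 | Week 12 |
|---|---|---|
| 1.0 | 0 | 0 |
| 1.5 | 0.03–0.08 SD | 0.06–0.12 SD |
| 2.0 | 0.05–0.14 SD | 0.12–0.22 SD |

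With b = 0 (severity does not affect healing) the shift is zero at every HR.

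**One case in full** (median 12 weeks, b = 0.5, HR 1.5, enhanced arm faster):
- Week 4: 78% of usual-care and 69% of enhanced ulcers are open, about 18 versus 6.5 people; shift 0.04 SD.
- Week 12: 49% and 36% are open, about 11.4 versus 3.4 people; shift 0.09 SD.
- Adding a true benefit of 0.1 SD in open ulcers brings the week-12 difference to about zero (0.007 SD).

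Over all scenarios with HR 1.5–2.0, 48–81% of the faster arm's ulcers are still scored at week 4 and 13–54% at week 12.

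**Against sampling error.** At week 12 the standard error is √(1/11.4 + 1/3.4) ≈ 0.62 SD. The difference detectable with 80% power is (1.96 + 0.84)·√(1/7 + 1/18) ≈ 1.25 SD for 7 versus 18 people, and about 1.62 SD for 4 versus 12.

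**Selection by who ulcerates.** As an extreme bound, suppose the enhanced arm's ulcers are the most severe 15/37 = 40.5% of those that would occur under usual care. The mean severity of that tail is about 0.957, so the score shifts by 0.7 × 0.957 ≈ 0.67 SD. If they are the mildest 40.5%, the shift is the same size in the other direction. Collecting scores after healing leaves this untouched.

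**The case against.** A wound-impact instrument is naturally given to people who have a wound, and impact while the wound is open is a coherent quantity. Duration and severity are reported separately. Quality of life after healing is not lost: the week-4 EQ-5D-5L has no healing condition, "Prior to each regular study visit, all participants will receive the EQ-5D-5L questionnaire", "and at 12 months also the SF-36". The generic and wound-specific measures can be read as complementary. After healing, some wound items would sit at the no-problem end, so unconditional collection would partly re-measure time to healing. The reporting of a secondary outcome in a subset is also ordinary material for an analysis plan that is not shown.

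Much of this stands, and it limits the point to one secondary outcome. It does not justify a significance test between groups formed after randomisation, which the article's general rule prescribes. A later analysis plan could drop the test but could not recover uncollected scores.

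A reader might infer that the enhanced arm is scored only on its worst ulcers and that the comparison is therefore biased against it. The documents do not support that. The stated hypotheses concern recurrence, adherence and cost-utility, with no expected difference in healing speed. Temperature monitoring is presented as detecting hotspots before an ulcer forms. At week 4 roughly half to four fifths of the faster arm's ulcers would still be scored. A modest true benefit in open ulcers can cancel the shift.

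**Conclusion.** The point holds as a minor one. The comparison is conditioned on two post-randomisation events, so it cannot carry a treatment claim whatever its direction. The healing-related bias is possible but not established. It needs both different healing speeds and a link between severity and healing, and the sizes above rest on assumed hazard ratios, medians, slopes and a 0.7 correlation. At 0.03–0.22 SD it is small beside the sampling error in so few people. Selection on who ulcerates could be larger, up to about 0.67 SD either way in the extreme. It would also be wrong to infer that dropping the healing condition makes the test valid. No primary outcome, sample size or QALY estimate is affected.

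**What to change.** State that the Cardiff Wound Impact Schedule will be presented descriptively by arm and healing status, with numbers completing it at each time, and with no between-arm significance test or efficacy claim. This answers both layers of selection and costs nothing.

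Where participants have not yet passed the time points, remove the healing condition so that every participant with an ulcer completes the schedule at weeks 4 and 12, with healing status recorded each time. This removes the healing-related selection only, so the descriptive status should remain. The cost is a small amendment and at most two short questionnaires in about 33 people, with some wound items scoring at the no-problem end after healing.
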